**Methods:**

This prospective study is being pursued within the framework of the DexaDays-2 study: a randomized controlled trial on neurobehavioral side effects in pediatric patients with ALL. A total of 105 children (3-18 years) undergoing ALL maintenance treatment at the Princess Máxima Center for Pediatric Oncology are included in this study. Sarcopenia/frailty assessments are performed before and just after a 5-day dexamethasone course. A subset of 50 children participating in the DexaDays-2 trial because of severe dexamethasone-induced neurobehavioral problems were assessed at 3 additional timepoints. The sarcopenia/frailty assessment consists of bioimpedance analysis (skeletal muscle mass [SMM]), handheld dynamometry (handgrip strength), Pediatric Quality of Life Inventory Multidimensional Fatigue Scale (fatigue), Timed Up and Go Test (TUG; walking speed), and physical activity questionnaires. To evaluate potential change in sarcopenia/frailty components after a 5-day dexamethasone administration, a paired Student t test or Mann-Whitney U test will be used. Because of the presence of repeated measurements, generalized linear mixed models will be used to estimate the effect of dexamethasone on sarcopenia and frailty outcomes. Multivariable regression models will be estimated to investigate associations between the assessment scores and patient and treatment-related factors.

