A total of 105 patients will undergo a physical frailty assessment before (T1) and after 5 days (T2) of dexamethasone administration (6 mg/m^2^ per day in 3 dosages). A subset of 50 children will be assessed at 3 additional timepoints (T3, T7, and T11), to observe the process of sarcopenia and physical frailty longitudinally. This subset comprised children participating in the DexaDays-2 randomized controlled trial based on the severity of their neurobehavioral problems. These 50 patients will receive physiological dosages of hydrocortisone or placebo during a 5-day dexamethasone treatment, and the cross-over will take place after 2 courses of dexamethasone treatment. The sample size is based on the DexaDays-2 study power calculation [40].

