#### Muscle Strength

Handgrip strength (kilogram) will be measured in sitting position with the elbow flexed at 90° using a hydraulic Jamar handheld dynamometer (Sammons Preston). During the measurement the child will be verbally encouraged to achieve a maximum performance. For both the dominant and nondominant hand the mean score of 3 repeats will be calculated. Raw results will be compared with population-based age- and sex-specific reference values [44]. Handgrip dynamometry showed good validity (intraclass correlation coefficients [ICCs] 0.73-0.91) with high reproducibility in children from the age of 4 years and has excellent test-retest reliability (ICC 0.91-0.93) [45,46], and the measurement was feasible in children with leukemia [47].

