#### Fatigue

Fatigue-related complaints will be assessed using the validated Dutch version of the Pediatric Quality of Life Inventory (PedsQL)-Multidimensional Fatigue Scale (MFS) [48,49]. This questionnaire consists of 3 scales: General Fatigue, Sleep/Rest Fatigue, and Cognitive Fatigue, resulting in subscores and in a total fatigue score. We will use parent proxy reports for children aged 2-4, 5-7, 8-12, and 13-18 years, as well as self-report versions for children aged 8-12 and 13-18 years. The results of PedsQL-MFS will be compared with Dutch normative values from the general population [48]. The internal consistency of the Dutch version of the PedsQL-MFS has been reported as satisfactory (Cronbach coefficient α >.70), test-retest reliability was good (ICC 0.68-0.84), and the interobserver reliability varied from moderate to excellent (ICC 0.56-0.93) [48]. The original version of PedsQL-MFS has been validated in patients with pediatric cancer, 50% of whom had ALL [49], and the Dutch version has been used previously in studies in children with ALL [28,50].

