#### Walking Speed

The TUG will be used to asses walking speed. A chair, without arm rests, allowing the child to sit with his feet flat on the floor and his hip and knees flexed at 90° will be used. The chair will be positioned at a 3-m distance from a wall. The child will be asked to get up from the sitting position and walk “as fast as he can, without running” to the wall and touch a self-chosen picture on the wall, turn around without using the wall for support, walk back to the chair, and sit down. During the test verbal instructions will be repeated and encouragements are made. Time is recorded from the “go” cue to when the child is sitting down in the chair. The mean time of 3 trials will be considered as the test result [51]. The results of the test will be compared with age-specific reference values [52]. The TUG has shown excellent test-retest reliability (ICC 0.80-0.98) and interobserver reliability (ICCs 0.86 to 0.99) in the pediatric population [53], and the measurement was feasible in children with leukemia [47].

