### Statistical Analysis

The results of the physical frailty assessments, that is, SMI, handgrip strength, self-reported fatigue, walking speed, and physical activity (component scores), will be reported as means and SDs, or as median and interquartile ranges if data are non-normally distributed. The frequency of sarcopenia and physical frailty, as well as the individual components at all timepoints will be reported in percentages and schematically visualized. A correlation matrix will be built to explore coherence between the additional measure TRF and the other frailty components.

To evaluate the potential change in frailty components after 5 days of dexamethasone administration, a paired Student *t* test or Mann-Whitney *U* test will be used depending on the distribution of the data.

To evaluate whether the mean scores from the frailty components change between T1, T3, T7, and T11, 1-way ANOVA will be employed.

To study the effect of dexamethasone administration at T1, T3, T7, and prior to T11 on sarcopenia, physical frailty, and each individual components, generalized mixed models will be estimated. These models incorporate correlations between repeated responses on the same individual. Patient-specific random intercept, age, weight, time since the start of therapy, and cumulative vincristine dosage will be included in the model.

Multivariable linear regression model will be estimated to investigate associations between the potential determinants (patient- and treatment-related factors, pharmacokinetics, and genetics) and the assessment scores at T1 and T2 (SMI, handgrip strength, self-reported fatigue, walking speed, TRF, and physical activity). Results will be presented as regression coefficients along with 95% CI.

Multivariable logistic regression models will be estimated to explore associations between the aforementioned potential determinants and the occurrence of sarcopenia and physical frailty at T1 and T2. Odds ratios along with 95% CIs will be estimated.

Statistical analyses will be performed using software packages R Statistics (version 1.0.143; R Foundation) and SPSS (version 26.0.0.1) for Windows (IBM).

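### Change across T1, T3, T7 and T11 is tested with a 1-way ANOVA, which treats repeated measurements on the same 50 children as independent groups and is severely conservative for small to moderate changes

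*Protocol article*

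**What the plan says.** Under Statistical Analysis, the protocol article states: "To evaluate whether the mean scores from the frailty components change between T1, T3, T7, and T11, 1-way ANOVA will be employed". Nothing in that sentence or around it marks the test as within-subject.

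The design section shows where the data come from: "A subset of 50 children will be assessed at 3 additional timepoints (T3, T7, and T11". All 105 children, including these 50, are assessed at T1.

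Elsewhere the article recognises the dependence. It names a paired t test for T1 versus T2. Of the mixed models in the paragraph after the ANOVA it says: "These models incorporate correlations between repeated responses on the same individual". The abstract gives the same reason: "Because of the presence of repeated measurements, generalized linear mixed models will be used". Those models are assigned to the effect of dexamethasone administration. Their listed terms are a patient random intercept, age, weight, time since start of therapy and cumulative vincristine dose. No timepoint factor is listed.

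**The concern.** A 1-way ANOVA with timepoint as the factor assumes that the groups are independent. Here each group is the same set of children, aged 3 to 18, who differ widely from one another in strength, speed and muscle mass. Those lasting differences cancel out of a within-child comparison. In the planned test they stay in the denominator of F. The test then rejects far less often than its nominal level and misses changes that the same data could show.

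This is the only test the article names for whether component means change over the longitudinal follow-up. A non-significant result from it would say little about whether a small or moderate change occurred.

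**Working it through.** The article gives no power, significance level, SD or relevant change for this analysis, and its sample size comes from the parent trial. There is therefore no stated figure to reproduce.

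**Inputs from the article**
- 50 children at T3, T7 and T11; 105 at T1.
- Test-retest coefficients, used as a proxy for within-child correlation r: fatigue, "test-retest reliability was good (ICC 0.68-0.84"; Timed Up and Go, "The TUG has shown excellent test-retest reliability (ICC 0.80-0.98"; handgrip, "excellent test-retest reliability (ICC 0.91-0.93". No coefficient is given for skeletal muscle index or physical activity.

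**Assumed inputs**
- Two-sided 5% level, total SD of 1, equal correlation between visits, complete data.
- Linear change, with means d × (0, 1/3, 2/3, 1), unless stated otherwise.

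**Why the test is conservative.** With n = 50 children and k = 4 visits:
- Between-visit sum of squares ~ (1−r) × χ²(3, λ), with λ = n Σ(m−m̄)² / (1−r).
- 1-way error sum of squares ~ (1−r) × χ²(147) + (1+3r) × χ²(49), on 196 df.
- The expected error mean square is [147(1−r) + 49(1+3r)] / 196 = 1.
- With no change, the expected between-visit mean square is 1−r.

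Under the null, F is therefore centred near 1−r rather than 1. At r = 0.68 it is centred near 0.32, yet it is compared with a critical value of 2.65 (3 and 196 df). A repeated-measures ANOVA divides by the within-child error, which is also 1−r, and so keeps its 5% level (3 and 147 df).

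**Example, d = 0.3.** Σ(m−m̄)² = 0.0225 + 0.0025 + 0.0025 + 0.0225 = 0.05, and 50 × 0.05 = 2.5. So λ = 2.5/0.32 = 7.8 at r = 0.68, 15.6 at r = 0.84 and 27.8 at r = 0.91.

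**Results, 50 children at every visit, linear change**

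| r | Size, 1-way | 0.2 SD: 1-way / repeated-measures | 0.3 SD: 1-way / repeated-measures |
|---|---|---|---|
| 0.50 | 0.18% | 2.2% / 20.5% | 8.8% / 43% |
| 0.68 | 0.006% | 0.5% / 31% | 3.8% / 63% |
| 0.84 | 0.000% | 0.02% / 57% | 0.7% / 92% |
| 0.91 | 0.000% | 0.001% / 84% | 0.1% / 99.6% |

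**Variations**
- Step change of 0.3 SD after T1, r = 0.5: 15% against 56%.
- Correlation that declines with distance (first-order autoregressive, adjacent 0.8), linear 0.3 SD: size 0.06%, power 6.9% against 37.8%, the latter from a Hotelling test.
- All 105 children at T1 and 50 later, extra children taken as exchangeable with the subset, r from 0.5 to 0.91: power of the 1-way test for 0.3 SD is 12-21% (linear) or 32-39% (step). Size stays below 1%.
- Linear change of 0.6 SD, 50 children, r from 0.5 to 0.91: power of the 1-way test is 76-83%.

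**The case against.** Four arguments count against the point.

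**The correlations may be too high.** Short-interval test-retest coefficients probably overstate the correlation over 15 weeks of chemotherapy. This stands, and it is why r = 0.5 and a declining correlation are shown. The gap narrows but remains several-fold.

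**The ANOVA may not be limited to the 50.** A reader might infer that the planned test almost never detects a change of 0.2-0.3 SD. The article does not support that without conditions. It does not say which children enter at T1, and with all 105 the power for 0.3 SD reaches 12-39%. It also sets no relevant change, so 0.3 SD is this review's choice.

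**A correlation-aware analysis is already planned.** The mixed models cover nearly the same timepoints for every component and include time since start of therapy. This tempers the consequence. A reader should not infer that the longitudinal data would have no valid analysis. But those models serve another question, and no test of change between visits is stated from them.

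**The wording may be shorthand for a repeated-measures ANOVA.** Possibly, but the text does not say so. If that was meant, the correction is one of wording.

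A reader might also infer a growth problem for handgrip, because "Handgrip strength (kilogram) will be measured in sitting position". The article does not establish one. It does not say that raw kilograms enter this test, and it mentions comparison with age- and sex-specific reference values. Any growth rate would have to be assumed.

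**Conclusion.** The concern holds in this limited form: the stated test does not fit the repeated-measures design. It runs far below its nominal level in every scenario examined and gives up much of the available power for small to moderate changes. The extreme figures, with power for 0.3 SD in the low single digits or below, require 50 children at each visit, a linear change and a within-child correlation of about 0.7 or more. Outside those conditions the loss is smaller but still substantial, and for linear changes near 0.6 SD the planned test performs adequately.

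The error runs towards missed changes, not false positives. It affects one secondary test in an observational study. It should be corrected because a finding of no change from this test could not be interpreted.

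**What to change.** Replace the 1-way ANOVA with a one-way repeated-measures ANOVA or, preferably, a linear mixed model for each component score with timepoint (T1, T3, T7, T11) as a categorical fixed effect and a random intercept per child. The mixed model also keeps children who miss a visit. State whether T1 uses the 50 subset children or all 105; the 50 are the natural choice for a within-child question.

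The cost is one change of wording and one model per component. A random-intercept model is already planned for the neighbouring question, and no new data are needed.

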So far, frailty has not been examined in children during ALL treatment nor has the relationship between dexamethasone and sarcopenia/frailty been investigated. Hence, the aims of this study are to estimate the occurrence of sarcopenia and physical frailty in children with ALL during maintenance therapy, to evaluate the effect of administering dexamethasone on sarcopenia and frailty (and their individual components) and to explore potential determinants associated with these outcomes. This paper describes the statistical design and methodology for this study.

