## Methods

### Study Design and Patient Recruitment

This prospective national observational cohort study is taking place at the Princess Máxima Center for Pediatric Oncology, Utrecht, the Netherlands. The children included in this study are participating in the DexaDays-2 study: a randomized controlled trial on neurobehavioral side effects in pediatric patients with ALL [40]. In that study, Dutch patients with ALL are eligible when they fulfill the following criteria: age 3-18, confirmed diagnosis of ALL, and inclusion in the Dutch Childhood Oncology Group (DCOG) medium-risk group of the ALL-11 protocol. Only patients between 3 and 18 years can participate as this was an inclusion criterion for the DexaDays-2 study, because the questionnaires used in that study are validated only for those ages. Children who reach the age of 3 years during maintenance therapy and are still due to receive 5 dexamethasone courses after their birthday (at least 15 weeks before the end of therapy) are also eligible. Exclusion criteria of that study are anticipated compliance problems, underlying conditions that affect the absorption of oral medication, uncontrolled infections, or any other complications that may interfere with administering dexamethasone treatment, insufficient command of the Dutch language, preexisting mental retardation, and hydrocortisone or risperidone use during the invitation to participate.

Our study on sarcopenia and frailty is being pursued within the framework of the aforementioned DexaDays-2 study. The latter consists of 2 parts: an identification study (including 2 timepoints: T1-T2) and a randomized controlled trial (T3-T11). The prospective observations of the current study are performed at a subset of these time points (Figure 1) during 15 weeks of the maintenance phase of ALL therapy.

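### The mixed model for the dexamethasone effect defines no exposure term and does not name T2; unless T2 outcomes are in it, the effect is separable from elapsed time only by assumption

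*Protocol article*

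**What the plan says.** The second aim, in the Introduction of the protocol article, is "to evaluate the effect of administering dexamethasone on sarcopenia and frailty (and their individual components").

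Under Study Design and Patient Recruitment, the visits are as follows: "A total of 105 patients will undergo a physical frailty assessment before (T1) and after 5 days (T2) of dexamethasone administration", and "A subset of 50 children will be assessed at 3 additional timepoints (T3, T7, and T11"). The 50 children in the subset are randomised between hydrocortisone and placebo with cross-over, and all of them take dexamethasone.

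The Statistical Analysis section gives three analyses that bear on change:

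- For the 5-day change: "To evaluate the potential change in frailty components after 5 days of dexamethasone administration, a paired Student" t test, or a Mann-Whitney U test.
- For the longer run: "To evaluate whether the mean scores from the frailty components change between T1, T3, T7, and T11, 1-way ANOVA will be employed".
- For the dexamethasone effect, generalized mixed models, with this stated purpose: "To study the effect of dexamethasone administration at T1, T3, T7, and prior to T11 on sarcopenia, physical frailty, and each individual components". Their content is then described: "Patient-specific random intercept, age, weight, time since the start of therapy, and cumulative vincristine dosage will be included in the model".

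The Abstract also rests the dexamethasone effect on mixed models, without a list of visits.

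**The concern.** A dexamethasone effect needs a contrast in exposure. No child goes without dexamethasone, so the contrast must come from within children: shortly after a course against before or between courses. T1-T2 is the only pair that the article states to bracket a course. The mixed-model sentence names neither T2 nor a variable that would carry this contrast, and its listed terms include time since the start of therapy.

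Aim 2 is at stake. If the model runs on T1, T3, T7 and T11 alone, growth, recovery or treatment over 15 weeks of maintenance could be reported as a dexamethasone effect, or a real effect could be absorbed by the time term. This matters most for sarcopenia and frailty as yes/no states. The paired test is stated for components only, so the mixed model is the only stated analysis of a dexamethasone effect on those two outcomes.

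A smaller point concerns weight as a covariate. If it is weight at each visit, dexamethasone may itself change it, and adjusting for it could remove part of the effect. Potential Determinants lists a weight Z-score at diagnosis, which has no such problem, but the model sentence does not say which is meant.

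**Working it through.** The article gives no figure to reproduce here, so the check asks whether a dexamethasone term can be told apart from time under each plausible coding.

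**Inputs.** The article gives a 15-week observation period. Its eligibility wording for children who turn 3 ("are still due to receive 5 dexamethasone courses after their birthday (at least 15 weeks before the end of therapy") implies 5 courses in 15 weeks. *Assumed:* courses every 3 weeks; T1 at week 0, T2 at week 5/7, T3 at week 3, T7 at week 9, and T11 at week 15 or at week 12 + 5/7 (just after the fifth course). Cumulative courses at T1, T3, T7 and T11 are then 0, 1, 3, 5.

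**Formula.** r is the within-child correlation of the dexamethasone term with time, and VIF = 1/(1 − r²).

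| Visits in model | Dexamethasone coding | T11 (week) | r | VIF |
|---|---|---|---|---|
| T1, T3, T7, T11 | cumulative 0, 1, 3, 5 | 15 | 1.00 | infinite |
| T1, T3, T7, T11 | cumulative 0, 1, 3, 5 | 12 + 5/7 | 0.994 | about 80 |
| T1, T3, T7, T11 | on/off 0, 0, 0, 0 | 15 | none (constant) | no estimate |
| T1, T3, T7, T11 | on/off 0, 0, 0, 1 | 12 + 5/7 | 0.76 | 2.4 |
| T1, T2, T3, T7, T11 | on/off 0, 1, 0, 0, 0 | 15 | −0.42 | 1.22 |
| T1, T2, T3, T7, T11 | on/off 0, 1, 0, 0, 1 | 12 + 5/7 | 0.27 | 1.08 |

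Row 1: weeks 0, 3, 9, 15 are exactly three times 0, 1, 3, 5. Row 2: sum of cross-products 37.96, sums of squares 98.95 and 14.75, so r = 37.96/√(98.95 × 14.75) = 0.994. Row 4: r = 6.54/√(98.95 × 0.75) = 0.76, and 1/(1 − 0.576) = 2.4. Row 5: r = −4.83/√(161.9 × 0.8) = −0.42. Row 6: r = 3.26/√(122.8 × 1.2) = 0.27.

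Row 4 looks harmless by its VIF, but the indicator equals 1 only at the last visit. With time as visit categories it is identical to the T11 effect, so the estimate is T11's departure from a straight line.

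**The other reading of the sentence.** If T1, T3, T7 and the point before T11 are dosing times, the courses at T3 and T7 still have no stated assessment directly after them. Their effects could appear only at later visits, after further courses, and so again move with elapsed time. T2 would then be essential, yet neither it nor an on/off term is specified.

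**Vincristine.** The VIFs for rows 5 and 6 are against time alone. Suppose vincristine is counted at each visit and one dose falls within each course (an assumption; the article gives no schedule). The counts in row 5 are then 0, 1, 1, 3, 5. Subtracting weeks/3 (0, 0.238, 1, 3, 5) leaves 0, 0.762, 0, 0, 0, which is 0.762 times the post-course indicator. The two are then exactly aliased. With simulated visit-time scatter (SD 0.5 week) at the visits after T2, the VIF was about 8 for row 5 and 12 for row 6.

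**Data involved.** Planned assessments are 105 + 105 + 3 × 50 = 360. T2 supplies 105 of them (29%) and is the only visit stated to follow a course directly.

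**The case against.** A reader might infer that the plan discards T2, but the text does not establish this. The sentence can be read as listing when dexamethasone is given; the qualifier before T11 suits a dosing time better than a visit, and T2, as a post-course assessment, would not belong in such a list. The Abstract does not exclude T2 either. This stands, so the point is conditional on T2 outcomes being absent.

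A reader might also infer that the effect is inestimable, with a correlation of exactly 1. That figure needs equal spacing, T11 at week 15 and cumulative-course coding, none of which the article states. The covariate is time since the start of therapy, which presumably differs between children at T1, so a random-intercept model could borrow between-child differences to estimate the time slope. Some number would come out, but it would rest on between-child and within-child trends being equal. Nor is T2 certainly the only post-course visit, since T11 may be one.

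Adjusting for time is not the fault. Without it, any trend would be read as a dexamethasone effect.

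Finally, exact coding is often left to a fuller document, and the T1-T2 change in components is tested separately. Both are fair. But the article does fix timepoints and covariates for this model, and on either reading what it fixes does not isolate the effect. The paired test does not reach binary sarcopenia and frailty, and reporting their percentages by visit is not a test of change.

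**Conclusion.** The point holds in conditional form. The article defines neither the outcome visits nor the exposure term of the model meant to answer Aim 2. If T2 outcomes are not included, the dexamethasone term is nearly or fully aliased with time (r about 0.99 to 1.00 for cumulative courses), constant across visits, or identified only through a linear trend (VIF about 2.4). If T2 is included with an on/off term, the acute effect separates well from a linear trend (VIF about 1.1 to 1.2), provided cumulative vincristine is not updated in step with the courses. A cumulative effect over maintenance stays confounded with time whichever visits are used, because every child is exposed.

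The figures rest on assumed 3-weekly courses and visit weeks. The conclusion that no dexamethasone-free comparison exists does not. Since the choice decides whether Aim 2 can be answered for sarcopenia and frailty, it should be settled before the analysis is run.

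**What to change.** - State that the mixed models use T1, T2, T3, T7 and T11.
- Define the dexamethasone term as a post-course indicator: T2 = 1, T11 coded by its true timing relative to the preceding course, other visits 0. The 0 codes assume that T3 and T7, like T1, are assessed before the course given there and that the acute effect has worn off by then; say so.
- Keep a linear time term.
- Fit the same model, with a logit link, to binary sarcopenia and frailty.
- If weight means weight at each visit, replace it with the Z-score at diagnosis. Hold cumulative vincristine at its T1 value, so that it cannot take over the post-course contrast.
- Report T1-T3-T7-T11 differences as change over maintenance, not as a dexamethasone effect.

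The cost is a change of analysis wording; the assessments are already part of the study. The downside is that the study can then claim only an acute effect of a course, not a cumulative one.

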Some possible study limitations have to be taken into account as well. We will only include children participating in the DexaDays-2 study, which could potentially lead to selection bias, as patients who experience dexamethasone-induced neurobehavioral problems could be more motivated to participate because in that trial they will receive a drug to potentially reduce these problems. Furthermore, the subset of 50 children that will be measured longitudinally comprises children participating in the DexaDays-2 randomized controlled trial based on the severity of their neurobehavioral problems. These patients will receive physiological dosages of hydrocortisone or placebo during a 5-day dexamethasone treatment, and the cross-over will take place after 2 courses of dexamethasone treatment. We do not know if this affects the occurrence of sarcopenia and physical frailty in this cohort, for example, whether children with dexamethasone-induced clinically relevant neurobehavioral problems also show more physical side effects. Besides, within the DexaDays-2 study patients aged 3-18 years were selected, which complicated selecting outcome measures suitable for all participants. We succeeded in selecting measurements that have previously been used and validated in pediatric populations indicating their usefulness; however, with the exception of the PedsQL-MFS, none of the measurements has been validated in pediatric oncology patients.

In conclusion, this study is designed to determine the occurrence and severity of sarcopenia and frailty components in children during the maintenance phase of ALL therapy, and to determine the effects of administration of high doses of dexamethasone on physical vulnerability. With this study we aim to create awareness about these potential risks in children with ALL, as well as expanding our knowledge for reducing further side effects.

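### The longitudinal models for T1, T3, T7 and T11 have no term for the randomised hydrocortisone/placebo exposure, so any hydrocortisone effect that persists to T7 or T11 is read as a dexamethasone or time effect

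*Protocol article*

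**What the plan says.** Under Study Design and Patient Recruitment, the Protocol article describes the parent trial as "an identification study (including 2 timepoints: T1-T2) and a randomized controlled trial (T3-T11"), and says of this study: "A subset of 50 children will be assessed at 3 additional timepoints (T3, T7, and T11"). On treatment in that subset it says "These 50 patients will receive physiological dosages of hydrocortisone or placebo during a 5-day dexamethasone treatment", and that "the cross-over will take place after 2 courses of dexamethasone treatment".

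The Statistical Analysis section gives the mixed model's purpose as follows: "To study the effect of dexamethasone administration at T1, T3, T7, and prior to T11 on sarcopenia, physical frailty" and each component. It then lists the terms: "Patient-specific random intercept, age, weight, time since the start of therapy, and cumulative vincristine dosage will be included in the model". A separate analysis covers the same visits: "To evaluate whether the mean scores from the frailty components change between T1, T3, T7, and T11, 1-way ANOVA will be employed". Neither has a term for hydrocortisone or placebo, and the Potential Determinants section does not list hydrocortisone. The Discussion mentions the cross-over among the limitations and adds "We do not know if this affects the occurrence of sarcopenia and physical frailty in this cohort", but no analysis follows from it.

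**The concern.** T7 and T11 are observed only in children who, since T3, have been taking a second glucocorticoid or its placebo during the courses whose effect is being estimated. The article's own Introduction names glucocorticoids as a class that causes muscle atrophy, so an effect on the outcomes cannot be dismissed beforehand.

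Before randomised treatment nobody is exposed. Afterwards, on average, part of the cohort is. Exposure therefore rises with study time. A random intercept cannot absorb a change within a child, and time since the start of therapy rises together with the exposure. What is at stake is the longitudinal part of the second aim: a change at T7 or T11 could be reported as due to dexamethasone or to time when part of it came from hydrocortisone.

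**Working it through.** The plan gives no effect size, SD or power for this analysis, so there is no figure of its own to reproduce. What can be worked out is what the omission does.

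**From the article:** 50 children; visits T1, T3, T7 and T11; hydrocortisone or placebo during dexamethasone courses; cross-over after 2 courses; T3-T11 inside the randomised part.

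**Assumed:** 1:1 sequences; T1 and T3 before any study drug; the two period-1 courses between T3 and T7 and the two period-2 courses between T7 and T11; ICC 0.7; no true dexamethasone or time effect. Let d be the hydrocortisone effect, in SD of a continuous component, still present at the next assessment. Let c be the fraction of d carried from period 1 to T11.

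**Shift when hydrocortisone is left out**
- T3: 0.
- T7: half the children were exposed, so 0.5d.
- T11: the other half were exposed, and the first half may carry over, so 0.5d + 0.5cd = 0.5d(1 + c).

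| d | T7 | T11, c = 0 | T11, c = 0.5 | T11, c = 1 |
|---|---|---|---|---|
| 0 | 0 | 0 | 0 | 0 |
| 0.2 | 0.10 | 0.10 | 0.15 | 0.20 |
| 0.5 | 0.25 | 0.25 | 0.375 | 0.50 |

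A simulation of 50 children agreed to within about 0.02 SD. With time as a linear term only (visits assumed at weeks 0, 3, 9 and 15), the spurious 15-week change was 0.11-0.20 SD for d = 0.2 and 0.29-0.53 SD for d = 0.5. The time covariate therefore takes up the hydrocortisone effect and does not remove it.

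**Shift after adding one hydrocortisone indicator and categorical visit.** The indicator's coefficient estimates d(1 - c/2). What remains is:
- T7: 0.5d - 0.5d(1 - c/2) = 0.25cd.
- T11: 0.5d(1 + c) - 0.5d(1 - c/2) = 0.75cd.

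Both are zero without carry-over. With d = 0.2 and c = 1, the T11 shift falls only from 0.20 to 0.75 × 0.2 = 0.15 SD. Adding a constant sequence effect leaves it at 0.15. Adding a term for hydrocortisone in the earlier period brings it to 0.

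**Precision**
- Change from T1, no indicator: variance 2(1 - 0.7)/50 = 0.012, SE 0.11.
- Indicator coefficient: each sequence group of 25 gives a mean T7-T11 difference with variance 0.6/25 = 0.024; half the difference between groups has variance (0.024 + 0.024)/4 = 0.012.
- Change at placebo, with indicator: 0.012 + 0.25 × 0.012 = 0.015, SE 0.12.
- With the carry-over term as well: SE at T11 about 0.25, from a generalised least squares fit under the same assumptions.

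**Estimability.** A none/hydrocortisone/placebo factor on top of a three-level period and a sequence term has 6 columns but rank 5, because none is the same as the pre-randomisation period. One indicator with categorical visit has full rank, with or without the carry-over term.

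**The case against.** **Timing.** A reader might infer that half the children have just finished hydrocortisone at T7 and at T11. The article does not say so; the timeline figure is not shown. Speaking of dexamethasone at T1, T3 and T7 but prior to T11 suggests assessments before a course. The eligibility rule equates 5 courses with at least 15 weeks, or about 3 weeks per course; with 5 days of dosing, the last hydrocortisone dose would be about 21 - 5 = 16 days past. This stands: only an effect that persists can bias these visits.

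**Effect size.** The dose is described as physiological, and nothing in the article anchors any value of d. This stands too. Inflation of the residual variance is also small: d²/4 is 0.01 to 0.04 SD² for d of 0.2 to 0.4.

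**Period.** Time since the start of therapy is in the model, so a smooth time trend is partly covered and period is not wholly missing. Treatment exposure is.

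**Disclosure.** The Discussion names the cross-over as a limitation. Its sentence goes on to give selection by severity of neurobehavioural problems as the example, so it is not a clear admission about hydrocortisone. In either case it adjusts nothing.

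**A condensed article.** The covariate list is not declared exclusive, and the parent trial's documents are not shown. But the article does set out the terms of this model, and a randomised co-treatment is a substantive omission from such a list.

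**Conclusion.** The omission is real and limited. As specified, the mixed model and the 1-way ANOVA cannot separate a lasting hydrocortisone effect from the dexamethasone or time effect at T7 and T11 in the 50-child subset. The T1-T2 comparison in 105 children and the T1/T2 determinant regressions are untouched, and so is T3 if, as assumed, no study drug is taken before it.

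The size is 0.5d at T7 and 0.5d(1 + c) at T11, given 1:1 sequences and the visit layout assumed above, with d and c unknown. It is zero if no effect persists, but the plan as written could not show that.

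Two stronger readings do not hold. One is that a bias of 0.1-0.2 SD has been established: that needs an assumed effect of 0.2-0.4 SD still present at the visits, and the article supports neither part. The other is that randomisation offers an unbiased correction at no cost: the simple adjustment is unbiased only without carry-over, and allowing for carry-over costs considerable precision. The figures apply to continuous components; for the binary sarcopenia and frailty outcomes the omission is the same but the sizes were not worked out.

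**What to change.** 1. Link the parent trial's allocation to the longitudinal data.
2. In every mixed model that uses T7 or T11 data, add categorical visit and one hydrocortisone indicator: 1 if the courses since the previous assessment were given with hydrocortisone, 0 otherwise. Do not add a separate none/hydrocortisone/placebo factor on top of period.
3. Report the T7 and T11 changes with the indicator set to placebo. Take the visit comparison from this model instead of the unadjusted 1-way ANOVA.
4. Add a sensitivity analysis with a term for hydrocortisone in the earlier period, or restricted to data through T7. A constant sequence effect is no substitute.

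**Cost.** No new measurements, but a data link. At an assumed ICC of 0.7, the SE of the T7 and T11 changes goes from about 0.11 to 0.12 SD in the main model, and to about 0.25 SD at T11 with the carry-over term. That sensitivity analysis will be imprecise and should be presented as such.
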